### Sample Size and Recruitment

Planned recruitment is approximately 1,300 patients. Recruitment is ongoing and will occur over 36 months. Enrollment began in March 2021.

To increase representativeness of selected sites, a large number of participating sites (up to 140) of different types (office- and hospital-based sites specialized in neurology), which are located geographically across Germany, are planned. To discourage physicians from selecting specific patients for inclusion in the study, they are instructed and trained to ask all eligible patients consecutively for their participation.

It is assumed that the persistence at year 5 will be 55% overall, including 50% of patients who switched to ozanimod treatment from another MS treatment and 55%−60% of treatment naive patients. A sample size of 1,331 patients is required to cover the estimated persistence rate of 0.55 with a 2-sided 95% confidence interval (CI) of 0.03 in each direction using the large sample normal approximation and after considering a dropout rate of 15%. This interval width is considered appropriate for correct description of the actual persistence rate on a descriptive level.

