#### Statistical Methods

According to the non-interventional design of the study, the statistical analyses are descriptive and exploratory. No statistical hypotheses are formulated. There will be no inferential testing, and no *P* value will be provided. Summary statistics for continuous variables will include number of observations available and number of missing values, minimum, maximum, median, mean, and standard deviation. Summary statistics for discrete variables will be presented with counts and percentages and number of missing variables.

The analysis set for the primary analysis will comprise all patients who received at least 1 dose of ozanimod during the study and for whom at least 1 postbaseline documentation is available. A subgroup analysis will be performed examining pretreatment with disease-modifying therapies (i.e., patients who are treatment-naive compared with patients who switched from another disease-modifying therapy to ozanimod).

If a patient is lost to follow-up, efforts will be undertaken to collect the data from the previous visit. Data management procedures will be implemented to limit the amount of non-reported data. Analysis methods for handling missing data (e.g., last observation carried forward, imputation, or sensitivity analyses) will be applied.

Treatment (e.g., dosage, duration of treatment, dose modifications, treatment interruptions, and concomitant medications) will be analyzed descriptively.

The analysis of the primary endpoint of persistence rate over 60 months in routine clinical practice will be calculated descriptively as percentage value at 60 months (i.e., the proportion of patients who are on continuous treatment with ozanimod at this time point), including corresponding 95% CIs calculated by the Clopper-Pearson method. A patient will be classified as non-persistent if a medication gap > 90 days occurs before the end of the 60-month documentation period. A sensitivity analysis will be performed evaluating patients who are lost to follow-up as “non-persistent.” The persistence rate will be evaluated by Kaplan-Meier methods over the entire study period (patients who are lost to follow-up will be right-censored).

The analysis of persistence rate at months 12, 24, 36, and 48 (secondary endpoint) will be calculated descriptively and summarized as the proportion of patients on continuous treatment at the respective time point, with corresponding 95% CIs.

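### The headline month-60 persistence is a crude proportion that leaves censoring of lost patients to a supporting analysis; at 15% lost it could shift by about as much as the planned ±3 points

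*Protocol article*

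**What the plan says.** All references are to the protocol article.

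- **Primary estimate (Statistical Methods).** Persistence over 60 months is "calculated descriptively as percentage value at 60 months (i.e., the proportion of patients who are on continuous treatment with ozanimod at this time point", with a Clopper-Pearson 95% interval. A patient becomes non-persistent through a medication gap of more than 90 days before the 60 months end.
- **Supporting analyses (same paragraph).** Counting lost patients as non-persistent is planned as a sensitivity analysis only. A Kaplan-Meier evaluation covering the whole study treats them differently: "patients who are lost to follow-up will be right-censored".
- **Missing data (same section).** Carrying the last observation forward, imputation and sensitivity analyses are named as examples. None is tied to the primary endpoint.
- **Analysis set (same section).** Patients with at least one dose and "for whom at least 1 postbaseline documentation is available".
- **Sample Size and Recruitment.** The planning value is given as "It is assumed that the persistence at year 5 will be 55% overall". The precision target for this value is "with a 2-sided 95% confidence interval (CI) of 0.03 in each direction using the large sample normal approximation". The resulting total is 1,331 patients, which includes a 15% allowance for dropout.
- **Study Setting and Treatment.** Permanent discontinuation leads to withdrawal from the study, so a documented stop is the endpoint event and not missing data.

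**The concern.** A patient who is lost while still on drug has an unknown month-60 status, and a simple percentage has to put that patient somewhere. The article gives two of the possible treatments to other analyses: non-persistent to the sensitivity analysis, censored to Kaplan-Meier. For the primary percentage, the text points to two others.

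- **Kept as persistent.** No gap is on record, so the gap rule is not triggered. Carrying the last observation forward does the same for a patient last seen on drug. Stops that happen after loss are never counted, so the estimate is too high.
- **Removed from the denominator.** The 15% inflation of the sample size suggests this. Patients who stop before they could be lost stay in as failures, while patients lost on drug disappear, so the estimate is too low.

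Both errors arise even when loss has nothing to do with stopping, and a binomial interval reflects neither. Persistence at month 60 is the only primary endpoint of a descriptive study, so the point estimate is itself the main result. The Discussion also cites prespecified handling of patients lost to follow-up as a protection against attrition bias. For the headline figure, the article fixes no such handling.

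**Working it through.** **1. The plan's own sample size.** Inputs from Sample Size and Recruitment: p = 0.55, two-sided 95%, half-width h = 0.03, dropout 15%.

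n = 1.96² × p(1 − p) / h²

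- With h = 0.03: n = 1,057, and 1,057 / 0.85 = 1,244. This is not the stated 1,331.
- With h = 0.029: n = 1,131, and 1,131 / 0.85 = 1,331. This matches exactly, so 0.03 looks like a rounded 0.029.

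The stated number is larger than the literal ±0.03 needs, so the precision target is met. The match also shows 1,131 patients as the evaluable number, which suggests that the 15% are taken out of the denominator. The Clopper-Pearson half-width at 55% is 2.9 points with 1,131 patients and 2.7 points with 1,331.

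**2. Effect of the rule for lost patients.** Assumptions: true month-60 persistence 55%; constant hazards of stopping and of loss; loss unrelated to stopping; 15% observed lost.

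- Cumulative stopping hazard over 60 months: L = −ln(0.55) = 0.598 (0.1196 per year).
- Cumulative loss hazard m solves m/(L + m) × (1 − e^−(L+m)) = 0.15. This gives m = 0.220 (0.0439 per year).
- On drug and followed at month 60: e^−(0.598 + 0.220) = 0.4416.
- Stopped and documented: 1 − 0.4416 − 0.15 = 0.4084.

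The three crude figures are then:

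- lost kept as persistent: 0.4416 + 0.15 = 59.2% (+4.2 points);
- lost excluded: 0.4416 / 0.85 = 52.0% (−3.0 points);
- lost counted as non-persistent: 44.2% (−10.8 points).

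Kaplan-Meier with censoring targets 55.0% under the same assumptions. The first two differ by 59.2 − 52.0 = 7.2 points, more than the full interval width of about 2 × 2.9 = 5.8 points.

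**3. Other loss rates, same method.** The 11.4% row takes 15% as the probability of loss if nobody stopped.

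| Observed lost | Kept as persistent | Excluded | Non-persistent |
|---|---|---|---|
| 5% | 56.4% (+1.4) | 54.1% (−0.9) | 51.4% (−3.6) |
| 10% | 57.7% (+2.7) | 53.0% (−2.0) | 47.7% (−7.3) |
| 11.4% | 58.1% (+3.1) | 52.8% (−2.2) | 46.8% (−8.3) |
| 15% | 59.2% (+4.2) | 52.0% (−3.0) | 44.2% (−10.8) |

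**4. Timing.** At 15% lost, letting stopping and loss fall earlier or later (Weibull shapes 0.6 to 1.5 for stopping, 0.3 to 5 for loss) gives shifts of +1.0 to +6.0 points (kept as persistent) and −0.8 to −6.7 points (excluded).

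**5. Precision of Kaplan-Meier.** With 1,300 patients and the hazards of step 2, the Greenwood variance is 0.55² × (0.1196/0.1635) × (1/0.4416 − 1) / 1,300. This gives a standard error of 0.0147 and a half-width of 0.029.

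**6. If loss is informative.** Using the step 2 proportions:

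- If all lost patients had stopped, the truth is 44.2%. Kaplan-Meier at 55% is 10.8 points too high, and exclusion at 52.0% is 7.8 too high.
- If half had stopped when lost and the rest followed the assumed hazard, the truth is 0.4416 + (0.55 − 0.4416)/2 = 49.6%. Kaplan-Meier is 5.4 points too high and exclusion 2.4.

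**The case against.** The strongest reply is that the plan already contains the remedies. A reader might infer that it cannot deal with loss to follow-up at all. The article does not support that, because the same paragraph plans Kaplan-Meier with censoring and a lost-as-non-persistent analysis. What remains is which estimate carries the primary label, and that choice is made in this article.

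A reader might also infer that the sponsor expects 15% lost to follow-up. The article says dropout and does not define it. It could include enrolled patients who never enter the analysis set, and loss within the set could be well below 15%. This stands, and at 5% lost the shifts are small.

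The two readings are not exhaustive. Imputation is named as a possible method, and the exact rule may sit in a full protocol or analysis plan that is not shown. This also stands, so the absence of a rule is not the point. The point is that a crude proportion was chosen as the headline, and both rules that the text suggests distort it.

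Kaplan-Meier is not safe either. Step 6 shows that it can be further from the truth than the exclusion it would replace when lost patients tend to have stopped. This is a real limit, and it is why the worst-case figure must stand next to it.

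The condition of a post-baseline documentation is a minor matter. Table 2, footnote a, provides for end-of-observation documentation after a permanent stop, so documented stoppers should remain in the set. A dosed patient without any later record would be censored near day 0 and add almost nothing to Kaplan-Meier. The condition matters only for whether the lost-as-non-persistent analysis is a full worst case.

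**Conclusion.** The concern holds as a moderate point. The headline estimate is fixed as a crude proportion, while the censoring of lost patients is assigned to a supporting analysis. If the 15% is loss to follow-up and the assumptions of step 2 apply, the headline would be shifted by +4.2 or −3.0 points depending on the rule used, against an interval of about ±3 points that does not show it.

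A reader might take 3 to 4 points as the established error. It is one scenario. The sign depends on the rule, the size falls to 1.4 points or less at 5% lost, and at 15% lost it runs from about 1 to 7 points with timing. Kaplan-Meier recovers the 55% only if loss is non-informative.

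The weight is moderate because the study is descriptive, has no hypothesis test, and already plans versions of all three analyses.

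**What to change.** 1. Designate the Kaplan-Meier estimate at month 60 as the primary result, with a Greenwood log-log 95% interval. Count time from first dose and censor lost patients at the last documented on-treatment date. Use the same estimate for months 12, 24, 36 and 48.
2. Report the crude proportion with its Clopper-Pearson interval beside it, and state how lost patients enter it.
3. Report the lost-as-non-persistent analysis next to both, in all patients with at least one dose and without the post-baseline condition, so that it is a true worst case.
4. State that the Kaplan-Meier figure assumes non-informative loss and is too high if lost patients tend to have stopped.

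The cost is wording, because the analyses are already planned apart from the wider patient set in item 3. The half-width of about 0.029 with 1,300 patients keeps the ±0.03 target. The change should be made before month-60 data exist.

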### Monitoring

An external steering committee is planned for data review, data evaluation, and publication in agreement with the leading principal investigator.

An interim analysis will be conducted after enrollment of 25% of the planned number of patients and will describe the baseline data. Thereafter, yearly interim analyses are planned.

AEs are collected during study site visits and via the patient portal, as described previously. All AEs occurring after the first dose of ozanimod until the end of the study (including the safety follow-up), whether related or not to ozanimod treatment, will be recorded and reported to the sponsor or its designee. AEs and SAEs are reported within 24 h. If it is discovered that a patient or female partner of a male patient is pregnant, this is reported to the sponsor within 24 h. SAEs associated with the pregnancy are reported within 24 h. Follow-up information on pregnancy outcomes is forwarded to the sponsor, even if the outcome becomes known after the end of the study.

Representatives of the sponsor and/or its delegates are permitted to visit all study site locations to assess the data quality and study integrity. On site, they review study files and, if allowed by local laws and regulations, patient medical charts to compare them with source documents, discuss the conduct of the study with the investigator, and verify that the facilities remain acceptable. In addition, the study may be evaluated by the sponsor's internal auditors and government inspectors, who are permitted access to CRFs, source documents, other study files, and study facilities.

## Discussion

OzEAN is an ongoing study to evaluate ozanimod treatment for RRMS in real-world clinical practice in Germany, with a large sample size, sophisticated methodology, and complex design involving endpoints related to multiple MS symptoms and functional consequences. The findings from this real-world evidence study will provide an important complement to the efficacy and safety results from highly structured randomized controlled trials (26), including phase 3 clinical trials (6, 7) and the ongoing open-label extension study of phase 1–3 trials (DAYBREAK) (27).

The eligibility criteria of OzEAN are less selective than those of the phase 2 and 3 clinical trials, allowing for inclusion of adults (≥18 years) of any age with RRMS who are eligible for ozanimod treatment and elect to initiate ozanimod treatment prior to and independent from study enrollment. There are no requirements in terms of relapse history, EDSS score, MRI parameters, or prior MS treatment. This is beneficial in 2 respects. First, it will be important to establish the efficacy and safety of ozanimod in a heterogeneous and extended population outside of the highly regulated confines of a clinical trial, in which patients are selected based on predetermined criteria that may not be met by a majority of patients in clinical care (28). Second, this will allow for characterization of patients prescribed ozanimod in real-world clinical practice. A question of interest is whether ozanimod is prescribed to patients newly diagnosed with MS, consistent with a shift toward earlier use of high-efficacy disease-modifying therapies (29), or reserved for patients previously treated with lower-efficacy agents (i.e., an escalation approach) (30).

The OzEAN study incorporates assessments of persistence and adherence to treatment. Persistence (remaining on continuous treatment) and adherence (taking treatment as prescribed) are important to treatment outcomes but tend to be poor in people with MS (31). Generally, persistence and adherence are better with oral disease-modifying therapies compared with injectables, but there are differences even among oral medications that can impact treatment success (31, 32). Assessment of persistence and adherence to ozanimod treatment is an important element of the OzEAN study and complements the TSQM v1.4 as another index of treatment satisfaction.

The efficacy outcome measures of the OzEAN study complement those of the phase 2 and 3 clinical trials (Table 5), which focused on traditional, physician-reported assessments of relapses (ARR) and disability progression (EDSS), MRI parameters (gadolinium-enhancing lesions, T2 lesions, and brain atrophy), and functional measures [the Multiple Sclerosis Functional Composite (MSFC)(33)), which comprises the Timed 25-Foot Walk (lower limb function and walking speed), Nine-Hole Peg Test (upper limb function and dexterity), and either the SDMT or the Paced Auditory Serial Addition Test (cognition) (4, 6, 7, 34, 35). QoL was assessed in the phase 3 studies using the MSQOL-54, but no other PROs were employed (6, 7). The value of assessing symptoms and consequences of MS that are viewed as important by patients, as well as the patient's perspective on treatment outcome and success, is increasingly recognized (26). The OzEAN study employs a number of PROs designed to evaluate not only QoL (MSQOL-54) and cognition (SDMT), but also treatment satisfaction (TSQM v1.4), patient-assessed disability (UKNDS), fatigue (FSMC), functioning at work and in other contexts (WPAI-MS v2.1), and costs associated with MS (MS-HRS v3.0). These PROs are valid, reliable, and responsive to change, with established thresholds for clinically meaningful change (Table 4).

**Table 5 T5:** Outcome measures in OzEAN compared with phase 2 and phase 3 studies of ozanimod.

	**Phase 2 (4)**	**Phase 3 SUNBEAM (7)**	**Phase 3 RADIANCE (6)**	**OzEAN**
**Clinical**				
ARR	X	X	X	X
Disability progression (EDSS)		X	X	X
MSFC		X	X	
T25FW		X	X	
9HPT		X	X	
SDMT		X		X
PASAT			X	
Persistence with therapy				X
**MRI**				
Gadolinium-enhancing lesions	X	X	X	X^a^
New or enlarging T2 lesions	X	X	X	X^a^
Brain atrophy		X	X	
**Patient-reported outcomes**				
MSQOL-54		X	X	X
TSQM v1.4				X
UKNDS				X
FSMC				X
WPAI-MS v2.1				X
MS-HRS v3.0				X
Adherence to therapy				X
**Safety and tolerability**				
AEs	X	X	X	X
Laboratory values	X	X	X	X^a^

*9HPT, Nine-Hole Peg Test; AE, adverse event; ARR, annualized relapse rate; EDSS, Expanded Disability Status Scale; FSMC, Fatigue Scale for Motor and Cognitive Functions; MRI, magnetic resonance imaging; MSFC, Multiple Sclerosis Functional Composite; MS-HRS v3.0, Multiple Sclerosis Health Resource Utilization Survey, version 3.0; MSQOL-54, Multiple Sclerosis Quality of Life-54; PASAT, Paced Auditory Serial Addition Test; SDMT, Symbol Digit Modalities Test; T25FW, Timed 25-Foot Walk; TSQM v1.4, Treatment Satisfaction Questionnaire for Medication, version 1.4; UKNDS, United Kingdom Neurological Disability Rating Scale; WPAI-MS v2.1, Work Productivity and Activity Impairment Questionnaire for Multiple Sclerosis, version 2.1*.

a *Only if available based on the local clinical routine assessments performed at the respective study site*.

To our knowledge, OzEAN is the first non-interventional study in MS to offer a patient portal. While use of the MSDS^3D^ data collection and management system has been incorporated into other real-world studies in MS (36–40), the expansion of this tool to include patient connection via the portal is intended to facilitate study participation, optimally inform patients, and support study patients' compliance. The aim of the patient portal is to obtain a high-resolution picture of the course of the disease with the highest possible data quality, independent from visits, through at-home documentation of digital PRO questionnaires (41). The patient portal complements and optimizes medical care in daily practice, as it enables the patient to play an active role in the study and to increase the e-health interaction between patient and study center.

This study has a number of further strengths. It represents the first collection of real-world data from patients with RRMS initiating treatment with ozanimod according to the SmPC. The results will broaden the understanding of ozanimod's safety and efficacy outside of controlled clinical conditions and in a patient population chosen based only on criteria outlined in the SmPC, and it will provide needed information to physicians and other health care providers on ozanimod treatment in routine clinical care. A high level of external validity can be expected, as the study sites and patient sample are selected to be representative of treatment and care in Germany.

There are also limitations. As OzEAN is an observational study, there is no randomization of patients, no blinding, and no control group. Outcome measures are limited to clinical assessments and PROs, with no MRI endpoints. Patient recall bias is a possible limitation, particularly with the long (6-month) intervals between assessments in the latter portion of the study. There is potential for selection bias with regard to participating sites and patients, as well as attrition bias, but measures are taken to minimize these issues, including participation of a large number of randomly selected sites of different types and locations across Germany, a large sample size, consecutive enrollment of eligible patients, and prespecified methods for handling missing data from patients lost to follow-up. Finally, the generalizability of the findings may be limited, as all of the study sites are located in Germany, a technologically advanced and predominantly racially/ethnically homogeneous country with a universal healthcare system.

## Conclusion

In summary, this is the first long-term, real-world study of ozanimod in patients with RRMS. These data will add to the safety and efficacy profile of ozanimod previously demonstrated in the phase 3 trials (6, 7) and the ongoing open-label extension study of phase 1–3 trials (DAYBREAK) (27) in patients with relapsing MS, and they will provide new information on endpoints not previously evaluated in ozanimod clinical trials. To our knowledge, this is the first non-interventional study utilizing a patient portal, which is expected to facilitate study participation and compliance, provide valuable information on PROs, and draw a high-resolution picture of the course of disease independent of study visits in a convenient way (41). Final long-term results are anticipated after study completion in March 2029; yearly interim analyses are planned after enrollment has reached 25%. The OzEAN study aims to assess the utility of ozanimod in clinical practice.

## Ethics and Dissemination

The required approvals from Ethics Committees, Independent Review Committees, Regulatory Authorities, and/or other local governance bodies were obtained before study initiation. The observational plan, patient questionnaires, and informed consent forms were reviewed and approved by the Independent Ethics Committee. The study was disclosed to the higher federal authority, to the German Association of Statutory Health Insurance Physicians, to the Central Federal Association of the Health Insurance Fund, and to the Association of Private Health Insurance Funds as required by §67 (6) German drug law. In accordance with local regulations, all patients provide written consent before enrollment. Investigators ensure that patients or their legally acceptable representatives are clearly and fully informed about the purpose of the study, potential risks, and the patient's rights and responsibilities when participating in this study.

